**Methods:**

The SPRING study is a multicenter, prospective, randomized, and open-label trial designed to compare the effectiveness and safety of PFO closure versus medication in the relief of migraines. The primary endpoint is the total cessation of migraines, as recorded in patient headache diaries during the follow-up period. Additional diagnostic tools include echocardiography with agitated saline contrast, transcranial Doppler, and routine laboratory measurements.

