**Fig. 1 Fig1:**
[figure not shown]
Flow chart of the study design. This figure explains the flow chart of the inclusion criteria screening and randomization

After a comprehensive review of inclusion and exclusion criteria, the investigators will proceed with the randomization and distribute headache diaries. Patients in the control group will be prescribed aspirin (100 mg daily) for 6 months and clopidogrel (75 mg daily) for 1 month. In contrast, patients in the treatment group will undergo percutaneous PFO closure in the catheterization laboratory.

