### PFO device closure

After local anesthesia, a 6-French MPA 2 catheter was inserted into the right heart system through the right femoral vein by placement of a 6-French vascular sheath. Under fluoroscopy, we measured the pressure in right atrium and pulmonary artery to exclude pulmonary hypertension related PFO. Then, we advanced the catheter through the PFO and anchor in the left inferior pulmonary vein. After accessing the size and location of the PFO, the MPA 2 catheter was exchanged for an 8-French or 9-French delivery sheath and a PFO closure device would be placed across the atrium septum under bedside TTE and fluoroscopy. After successful implement, patients were prescribed same medication of Aspirin 100 mg qd for 6 months and clopidogrel 75 mg qd for 1 month, and would be usually discharged home in the next day.

The success of the percutaneous PFO closure procedure will be defined as implantation of the PFO device without any major complication including death, stroke, or any complication that requires surgical or endovascular treatment.

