### Study outcomes

Primary and secondary endpoints are presents in Table 2. The outcomes of the migraine changes are adjudicated based on the headache diary data. The total days of migraine is defined as migraine frequency per month plus migraine average duration, divided by 24, round up to nearest integral. The definition of responder rate is the percentage of patients who have at least 50% reduction of monthly migraine attacks from their baseline. Other efficacy measures include migraine severity, as assessed by the HIT-6 scale [17], and quality of life alterations, determined by the SF-36v2 questionnaire [18]. These changes would be also analyzed the relationship with a successful PFO closure and residual shunt.

**Table 2 Tab2:** Primary and secondary endpoints

Primary endpoint
Complete cessation of migraine during the follow up.
Secondary efficacy endpoints
Mean reduction of monthly migraine attacks. Mean reduction of monthly migraine days. Responder rate.
Secondary safety endpoints
All-cause mortality. Peripheral embolism. New-onset arrhythmia warranting intervention. New-onset myocardial infarction. Other complications related to PFO closure procedure, device and antiplatelet drugs. Other side effects associated with the drugs used in the study.

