### Data management and monitoring

All clinical data will be de-identified and stored in an electronic data capture system. The Headache Diary Review Committee, blinded to the randomization, will oversee the calculation and recording of migraine severity and frequency. The Independent Event Committee and the Data Safety Monitoring Board will ensure the integrity of the data and monitor the safety of the participants.

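### The last two safety endpoints are defined by assigned cause and overlap on drugs both arms take, so neither gives a clean between-arm comparison of bleeding

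*Protocol article*

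**What the plan says.** Table 2 (Study outcomes) lists six secondary safety endpoints. The first four are all-cause mortality, peripheral embolism, new arrhythmia needing intervention and new myocardial infarction. These are named clinical events, and none depends on the cause assigned to it. The last two do: "Other complications related to PFO closure procedure, device and antiplatelet drugs. Other side effects associated with the drugs used in the study". The first sentence of that quote is the fifth line of the list and the second is the sixth.

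The drugs are described in two places. For the control arm, the Study protocol section states: "Patients in the control group will be prescribed aspirin (100 mg daily) for 6 months and clopidogrel (75 mg daily) for 1 month". For the closure arm, the PFO device closure section states that after implantation "patients were prescribed same medication of Aspirin 100 mg qd for 6 months and clopidogrel 75 mg qd for 1 month". The article names no other study drug.

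On blinding, the abstract states: "The SPRING study is a multicenter, prospective, randomized, and open-label trial". Under Data management and monitoring, one committee is described as blinded, and its remit is headache data: "The Headache Diary Review Committee, blinded to the randomization, will oversee the calculation and recording of migraine severity and frequency". For safety the text reads: "The Independent Event Committee and the Data Safety Monitoring Board will ensure the integrity of the data and monitor the safety of the participants".

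**The concern.** The two lines do not separate the risks that a reader of the safety results needs to tell apart.

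First, an event caused by aspirin or clopidogrel meets both descriptions. Only the undefined terms complication and side effect distinguish them.

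Second, the fifth line adds together risks that only the closure arm can have and a drug risk that both arms share. A difference between arms on that line cannot show how much is due to the device or procedure.

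Third, bleeding has no line of its own, although recent bleeding or a high bleeding risk excludes a patient (Table 1). A non-fatal bleed therefore reaches the safety endpoints only through these two lines, and only after someone has assigned a cause. More causes are available after closure (procedure, device, drug, unrelated) than in the control arm (drug, unrelated). Where treatment is known, the same kind of bleed can be filed differently by arm.

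The trial is presented as a comparison of effectiveness and safety. At stake is whether its report can state plainly how bleeding compared between the randomised groups.

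**Working it through.** The article gives no bleed rate and no expected safety count, so there is no figure of the plan's to reproduce. The check has two parts.

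**1. Where a non-fatal bleed on aspirin or clopidogrel can be filed, from the wording of Table 2**

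| Assigned cause | Closure arm | Control arm |
|---|---|---|
| Procedure or device | fifth line | not possible |
| Antiplatelet drug | fifth or sixth line | fifth or sixth line |
| Unrelated | neither line | neither line |

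The top row exists in one arm only. The middle row has two possible destinations in both arms. Neither line therefore collects all bleeds on the same footing in both groups.

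**2. How far filing alone could move a comparison (illustration)**

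Inputs: 220 patients per arm (Sample size and statistical considerations); two-sided P < 0.05, which the article applies to all analyses. Assumptions, not in the article: the true bleed risk is equal in both arms at 10%, 5% or 2%; half of the closure-arm bleeds are filed as procedural; all remaining bleeds in both arms are filed as drug side effects.

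For counts a and b, with 220 per arm:

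- pooled proportion p = (a + b)/440
- SE = √[p(1 − p) × 2/220]
- z = [(b − a)/220]/SE

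At 10%, true bleeds are 22 v 22, and drug side effects read 11 v 22:

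- p = 33/440 = 0.075
- SE = √(0.075 × 0.925 × 2/220) = 0.0251
- z = 0.05/0.0251 = 1.99; two-sided P = 0.046 (uncorrected chi-square)
- with continuity correction P = 0.070; Fisher's exact test P = 0.069

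| Assumed true rate | True bleeds per arm | Filed as drug side effects (closure v control) | Uncorrected P |
|---|---|---|---|
| 10% | 22 | 11 v 22 | 0.046 |
| 10%, one fewer refiled | 22 | 12 v 22 | 0.074 |
| 5% | 11 | 5 v 11 | 0.13 |
| 2% | 4 (4.4 rounded) | 2 v 4 | 0.41 |

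The direction is the same in every row: with equal true risk, filing any closure-arm bleed as procedural lowers that arm's drug side-effect count. Nominal significance appears only in the first row, and only without a correction.

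**The case against.** The strongest reply is that this is a condensed article. Event definitions, causality rules, counting rules and a committee charter normally sit in the full protocol or analysis plan, and their absence here is no fault. That stands. It does not dispose of the point, which concerns the endpoint lines as they are written: a line that pools device and drug events stays pooled however carefully causes are judged.

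An Independent Event Committee and a Data Safety Monitoring Board exist, and independent review is the usual check on investigator attribution. The committee may well reduce the problem. The article states neither that it is blinded nor that it judges cause, so its effect is unknown. Even blinded adjudication would leave the fifth line merged.

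A reader might infer that the same bleed will be counted twice. The document does not support that. Both lines begin with the word *Other*, so the last can be read as a residual class, and nothing says events are entered under both or summed. On that reading the sixth line is almost empty, because every named study drug is an antiplatelet.

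A reader might also infer that any difference in drug side effects would be mostly attribution. That goes too far. A control-arm bleed can also be judged unrelated. Exposure need not be equal either: closure patients are given the drugs after successful implantation, and the Study design section states the control drugs without durations. Filing half of the closure-arm bleeds as procedural is itself a strong assumption, since patients usually go home the next day while aspirin continues for six months.

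Finally, the four other safety endpoints are untouched, and the listed chi-square comparisons do not name safety endpoints; only the general significance rule reaches them.

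**Conclusion.** The point holds for how the endpoints are defined. Both lines are entered by assigned cause, they overlap on drugs that both arms receive, the fifth merges closure-only and shared risks, and bleeding is not named. As written, neither gives a clean randomised comparison of bleeding.

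The size cannot be fixed from the article. The illustration reaches nominal significance only at an assumed 10% bleed rate, with half of closure-arm bleeds refiled and an uncorrected test. It shows that a false difference is possible, not that one is likely. Certain double counting and a demonstrated bias are not supported.

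The point affects how safety is interpreted and leaves the primary result alone. It is minor to moderate and cheap to mend.

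**What to change.** Replace the last two lines of the safety list in Table 2 by:

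- (a) Procedure- and device-related complications, reported descriptively for the closure arm as a rate with a 95% confidence interval.
- (b) Bleeding and other adverse events by type, regardless of assigned cause, counted once per patient from randomisation in both arms and compared between arms. Assigned cause is shown as a descriptive column only.

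The cost is two table lines and the matching table shells, with no new visits or procedures. There are two downsides. All-cause counts will include some background events unrelated to treatment, in both arms. Non-serious bleeds must also be recorded in both arms, whereas the Follow up section mentions only serious adverse events. The existing drug side-effect endpoint already implies that wider recording.

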### Data management and monitoring

All clinical data will be de-identified and stored in an electronic data capture system. The Headache Diary Review Committee, blinded to the randomization, will oversee the calculation and recording of migraine severity and frequency. The Independent Event Committee and the Data Safety Monitoring Board will ensure the integrity of the data and monitor the safety of the participants.

### Sample size and statistical considerations

This was a randomized controlled study with PFO blocking group as the intervention group and drug treatment group as the control group. Migraine frequency (monthly migraine days), improvement in migraine frequency, severity (migraine scale score) and quality of life score were the outcome indicators. According to previous reports, the frequency of migraines treated with medication was 6.5 ± 2.4 days/month. The migraine HIT-6 score was 66.2 ± 5.1; After treatment, the number of migraine attacks per month can be reduced by 25%; SF12 quality of life score increased by 1.2 ± 6.9 points after treatment. The frequency of migraine was expected to decrease by 0.6 days in PFO occlusion group. Migraine scale HIT-6 score decreased by 1.5 points; After treatment, the number of migraine attacks per month can be reduced by 50%; SF12 quality of life score improved by 4.2 points after treatment. The test level was set as bilateral α = 0.05, and the assurance was 80%. PASS 15.0 software was used to calculate the required sample size of 113, 183, 60 and 156 cases in each group based on the above four observation indicators. Taking the maximum sample size and considering 20% of the cases of loss and refusal to visit, the final requirement was 220 cases in the PFO blocking group and 220 cases in the drug treatment group.

The primary endpoints will be analyzed across different analysis sets: Intention-to-Treat, per-protocol, and as-treated, with the primary analysis set being Intention-to-Treat. Categorical variables will be described using rates and composition ratios. Group differences in variables such as migraine termination, sociodemographic factors, migraine incidence rate, changes in migraine characteristics (with or without aura and their changes), effective closure rates, or residual leakage will be compared using the chi-square test. Continuous variables will be characterized based on their data distribution, utilizing means, standard deviations, medians, and interquartile ranges. Group differences in variables such as sociodemographic factors, severity and frequency of migraine attacks, and quality of life scores derived from the SF-36v2 questionnaire will be compared using t-tests or the Wilcoxon test.

Additional analysis will involve covariance analysis to account for factors significantly influencing the observed indicators. Different centers will be treated as random effects, and generalized linear models will be employed to further control for the potential impact of center effects. Stratified analysis will be performed based on factors such as gender and age. Predefined subgroups will include migraine with or without aura. Survival function estimation will be conducted using the Kaplan–Meier method. Relevant covariates will be controlled for using the Cox proportional hazards model, and truncated data will be analyzed accordingly.

For all analyses, a two-tailed *P* value < 0.05 was used as the criterion for statistical significance. Analyses were performed using SPSS 22 software (IBM Corp., Armonk, NY, USA).

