### Study design

The Spring study is a multicenter, randomized and open-label trail comparing the effectivity and safety of PFO closure vs medicine in alleviating migraine, with a follow-up period of 12 months (ClinicalTrials.gov ID NCT04946734). The trial is performed in 21 centers in China and has been approved by all local ethics committees. Our hypothesis posits that, compared to medication alone (clopidogrel 75 mg q.d. and aspirin 100 mg q.d.), PFO closure accompanied by one months of clopidogrel (75 mg q.d.) and six months of Aspirin (100 mg q.d.) will be more effective in completely ceasing migraines. Patient recruitment is expected to be completed by the end of 2024, with final results anticipated in 2025.

Patients with migraine and PFO were included in this study. Participant inclusion and exclusion criteria are presented in Table 1.

**Table 1 Tab1:** Inclusion and exclusion criteria

Inclusion criteria
1. Subject is aged between 16 and 60 years old.
2. Subject is diagnosed of PFO with right-to-left shunt, confirmed by Transthoracic echocardiography (TTE) or transesophageal echocardiography (TEE) with agitated saline contrast.
3. Subject is diagnosed of right-to-left shunt, confirmed by transcranial doppler with agitated saline contrast.
4. Subject is diagnosed of migraine without identifiable cause of headache.
5. Subject signs an informed Consent Form and is willing to participate in follow-up visits; 6. Primary and secondary endpoints.
Exclusion criteria:
1. Subject is diagnosed of headache with clear etiology.
2. Subject had cerebral hemorrhage, bleeding events in other organs within 3 months or was in high risk of bleeding.
3. Subject presents with ischemic lesions as indicated by brain CT/MR imaging.
4. Subject is diagnosed of hepatic insufficiency: ALT or AST > 3 × ULN at the screening visit.
5. Subject is diagnosed of moderate to severe renal insufficiency: eGFR < 30 ml/min/1.73m2 at the screening visit.
6. Subject has uncontrolled arrhythmia with clinical significance within 90 days.
7. Subject is diagnosed of unstable angina, severe coronary atherosclerosis or myocardial infarction within 90 days.
8. Subject is diagnosed of pulmonary artery embolism, peripheral artery embolism or deep Vein Thrombosis.
9. Subject cannot follow the study procedure due to other acute or chronic diseases.
10. Subject is pregnant or lactating.
11. Subject is under other RCT.
12. Subject has a life expectancy < 1 year.

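### The stated 80% power belongs to four other outcomes; complete cessation, the sole primary endpoint, has no assumed rate, difference or power, so the adequacy of N for it is unknown

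*Protocol article*

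**What the plan says.** Three places in the protocol article make cessation the trial's question. The abstract says "The primary endpoint is the total cessation of migraines, as recorded in patient headache diaries during the follow-up period". The hypothesis under Study design is that closure "will be more effective in completely ceasing migraines". Table 2 lists a single primary endpoint: "Complete cessation of migraine during the follow up". This is a yes/no outcome, and the statistical section plans a chi-square test for it.

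The section Sample size and statistical considerations names a different set: "Migraine frequency (monthly migraine days), improvement in migraine frequency, severity (migraine scale score) and quality of life score were the outcome indicators". It then gives inputs for monthly migraine days ("the frequency of migraines treated with medication was 6.5 ± 2.4 days/month"; "The frequency of migraine was expected to decrease by 0.6 days in PFO occlusion group"), HIT-6 (66.2, SD 5.1, a fall of 1.5 points), reduction in attacks (25% v 50%) and SF12 (+1.2, SD 6.9, v +4.2). The error levels follow: "The test level was set as bilateral α = 0.05, and the assurance was 80" (per cent). The four results are 113, 183, 60 and 156 per group. The largest is taken, and an allowance of 20% for loss gives 220 per group.

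**The concern.** A power statement holds only for the outcome, effect and test it was computed for. Here the only power figure in the article sits beside a primary endpoint that played no part in the calculation. Taking the largest of four sample sizes protects those four outcomes and says nothing about a fifth. The outcome that set N, HIT-6, is not in Table 2 at all; the text under Study outcomes treats it as a further efficacy measure.

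At stake is how the primary result will be read. If the cessation comparison is not significant, a reader who sees 80% in the sample-size section may take it for a well-powered negative result, and nothing in the article supports that. The Discussion also suggests that small samples may have contributed to earlier trials missing their endpoints, and offers a larger sample as a remedy. For this trial's own primary endpoint, that argument has no calculation behind it.

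**Working it through.** **1. Endpoints against sizing.**

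| Outcome | Place in Table 2 | n per group in the sizing |
|---|---|---|
| Complete cessation | Primary (the only one) | none |
| Monthly migraine days | Secondary | 113 |
| Reduction in attacks | Secondary | 60 |
| HIT-6 | Not listed | 183 (sets N) |
| Quality of life (SF12) | Not listed | 156 |

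**2. Reproducing the figure that sets N.** Inputs from the sample-size section: HIT-6 difference 1.5, SD 5.1, two-sided 0.05, power 80%.

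n = 2(1.960 + 0.842)² × SD²/δ² = 2 × 7.849 × 26.01/2.25 = 181.5, so 182 by normal approximation. The two-sample t-test gives 183, as stated.

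The loss allowance is 183 × 1.2 = 219.6, so 220, as stated. If 20% of 220 are lost, 220 × 0.8 = 176 per arm remain. HIT-6 power at 176 is about 79%.

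**3. The other printed inputs.** Reading the 0.6 days as the between-group difference, in the same way that reproduces HIT-6: 2 × 7.849 × 2.4²/0.6² = 251.2, so 252, or 253 by t-test, against 113 stated. On the printed inputs, migraine days and not HIT-6 would give the largest n. For SF12, 4.2 − 1.2 = 3.0 with SD 6.9 gives 85 by t-test, against 156 stated. The 60 for attacks is close to the 58 obtained when 25% and 50% are treated as two proportions.

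**4. Power for cessation.** The article gives no cessation rates, so all rates below are assumptions. For control and closure rates p₁ and p₂ and n per arm, the test rejects when |p̂₁ − p̂₂| / √(2p̄(1 − p̄)/n) > 1.96, where p̄ is the pooled observed proportion. This is the chi-square test without continuity correction. Power is the sum of the two binomial probabilities, multiplied together, over all pairs of counts that reject.

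| Control v closure | Power, 176 per arm | Power, 220 per arm |
|---|---|---|
| 10% v 15% | 30% | 36% |
| 5% v 10% | 43% | 51% |
| 3% v 8% | 55% | 64% |
| 1% v 6% | 77% | 86% |
| 3% v 11% | 86% | 93% |
| 5% v 15% | 90% | 95% |

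Closure rate needed for 80% power, by the same exact method:

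| Control rate | 176 per arm | 220 per arm |
|---|---|---|
| 1% | 6.3% | 5.4% |
| 3% | 10.2% | 9.3% |
| 5% | 13.5% | 12.4% |
| 10% | 20.6% | 19.3% |

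As a cross-check, the usual two-proportion formula asks for 141 per arm at 5% v 15%, 159 at 3% v 11%, 211 at 1% v 6%, 435 at 5% v 10% and 686 at 10% v 15%. These fall on both sides of the 183 planned.

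**The case against.** The sample-size section ties its calculation to the four indicators and never says that the trial has 80% power for cessation. That stands: the fault is a missing justification for the primary endpoint, not a false power statement about it.

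A reader might infer that the trial is underpowered for cessation. The article does not support this. The 5-point differences in the table all miss 80% at 176 per arm, but nothing in the article makes 5 points the relevant difference, and wider gaps such as 3% v 11% or 5% v 15% exceed 80%. Nor can one argue that cessation must be uncommon. The Discussion mentions an increase in cessation in a pooled analysis without giving rates, and says that this trial, unlike earlier ones, does not require preventive medication before closure.

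The denominator is also open. The primary analysis set is intention-to-treat, and the article does not say how missing diaries are counted, so the analysed number could lie between 176 and 220. At 220, 1% v 6% reaches 86%. Both columns are therefore shown.

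Finally, type I error and the effect estimate are unaffected, a confidence interval will show the precision achieved, and recruitment was expected to finish by the end of 2024. These points limit the remedy to disclosure but do not remove the gap. Condensation does not explain it either: the section prints inputs, error levels, software, four results and the loss allowance, and attributes the final number to those four indicators. The mismatch between SF12 in the sizing and SF-36v2 as the collected instrument is a separate matter, since SF12 did not set N.

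**Conclusion.** The point holds in this form: the trial's only power figure was computed for four outcomes that do not include the primary endpoint, and N rests on the stated HIT-6 figure. For complete cessation no rate, difference or power is given, so whether 220 per group is adequate for the primary question is unknown. Over the assumed rate pairs, exact power at 176 per arm runs from 30% to 90%, so 80% is neither shown nor excluded. These figures assume two-sided 5%, an uncorrected chi-square test, equal arms and the rates in the table. The detectable closure rates (for example 13.5% against 5% at 176 per arm) are the more useful summary, because they need only a control rate.

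**What to change.** Keep 220 per group. In the sample-size section:

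- State that the 80% applies only to the four indicators, and that N came from the stated HIT-6 result of 183.
- Give an assumed control cessation rate with its source, and the difference in cessation considered meaningful.
- Report the resulting power or detectable difference for the chi-square test at 176 and 220 per arm, over a range of rates that falls on both sides of 80%.
- While rewriting, recheck the other printed inputs. Migraine days at 0.6 with SD 2.4 need about 253 per group and not 113, and HIT-6 power at 176 is about 79%. Otherwise the new text would carry forward a derivation that cannot be reproduced.

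The cost is rewording. No extra patients are needed, and no endpoint, test or procedure changes. The power stated for the primary endpoint may prove less favourable than 80%.

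### Quality of life is sized on the SF12 but measured and tested with the SF-36v2, and the stated 156 per group does not follow from the printed SF12 inputs

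*Protocol article*

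**What the plan says.** In the section Sample size and statistical considerations, quality of life is one of four indicators used for sizing. Its inputs are all on the SF12. For medication: "SF12 quality of life score increased by 1.2 ± 6.9 points after treatment". For closure: "SF12 quality of life score improved by 4.2 points after treatment". The test is two-sided at 0.05 with 80% power, and the result is a "required sample size of 113, 183, 60 and 156 cases in each group based on the above four observation indicators". Quality of life is the last indicator listed, so 156 is its figure. Enrolment then follows from "Taking the maximum sample size and considering 20% of the cases of loss and refusal to visit", which leads to "220 cases in the PFO blocking group and 220 cases in the drug treatment group".

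The other two statements name a different instrument. Study outcomes refers to "quality of life alterations, determined by the SF-36v2 questionnaire". The analysis paragraph, in the same section as the sample size, says that "quality of life scores derived from the SF-36v2 questionnaire will be compared using t-tests or the Wilcoxon test".

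The SF12 appears only in the sample-size paragraph. Nothing says that it is administered, that an SF12 score is derived from the SF-36v2, or that the SF12 assumptions are meant to carry over.

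**The concern.** A sample size for a mean difference holds for a score with the stated difference and SD. Here those two numbers belong to one instrument, and the measurement and test belong to another. Unless the plan says how the two are linked, the 80% power is not a property of the test that will be run.

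At stake is how the quality-of-life result is read. Someone looking at the final comparison will take the protocol as having planned 80% power to detect a 3.0-point difference. The document supports that for no SF-36v2 score, and the printed figures do not support it for the SF12 either.

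**Working it through.** **Inputs, all from the sample-size paragraph.** SF12 change +1.2 with medication and +4.2 with closure; SD 6.9; two-sided alpha 0.05; power 80%; equal groups. I read the value after the ± sign as the SD of the change, apply it to both groups, and take the difference as 4.2 − 1.2 = 3.0.

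**Formula.** n per group = 2 × (z₀.₉₇₅ + z₀.₈₀)² / d², with d = difference / SD and (1.960 + 0.842)² ≈ 7.849.

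**Step 1: does the method reproduce a figure that the plan states?** For HIT-6, d = 1.5 / 5.1 = 0.294, so n = 15.70 / 0.0865 = 181.5, rounded up to 182. The t-test version gives 183, which is the stated figure. The method is therefore the plan's own, at least for that indicator.

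**Step 2: quality of life by the same method.** d = 3.0 / 6.9 = 0.435, so n = 15.70 / 0.189 = 83.0, rounded up to 84. The t-test version gives 85. The plan states 156.

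**Step 3: can another reading give 156?**

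| Reading | n |
|---|---|
| One-sided | 66–67 per group |
| Alpha 0.025 | 101 per group |
| 90% power | 112–113 per group |
| 95% power | 138 per group |
| Total over both groups | 168 |
| Wilcoxon efficiency loss | about 88–97 per group |
| Difference 4.2 | 43–44 per group |
| Difference 1.2 | 520 per group |

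None gives 156. The t-test formula does give 156 with a difference of 2.2 and SD 6.9. An SD of about 9.5 with a difference of 3.0 also fits. The document prints neither, so the source of 156 is unknown.

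**Step 4: power at 156 per group with the printed inputs.** d × √(n/2) = 0.435 × √78 = 3.84; 3.84 − 1.96 = 1.88; Φ(1.88) ≈ 0.97. That is about 97%, not 80%.

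**Step 5: does this move enrolment?** The largest of the four figures is 183, and 183 × 1.2 = 219.6, which rounds to 220. The quality-of-life figure does not enter, whether it is 156 or 85.

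**Step 6: what can be said about the SF-36v2?** The document gives no SF-36v2 mean, SD or expected difference, so neither a sample size nor a power follows. Only the detectable standardised difference at 80% power can be stated. If 20% are lost, 220 × 0.8 = 176 per group remain, and the detectable value is 2.80 × √(2/176) ≈ 0.30 SD. With all 220 it is 2.80 × √(2/220) ≈ 0.27 SD.

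**The case against.** The case for leaving this alone is that little hangs on it. Quality of life is not in Table 2; Study outcomes places it among further efficacy measures. HIT-6 sets enrolment. An exploratory comparison can be read from its estimate and confidence interval without a power statement. All of that stands, and it limits the point to a correction of the quality-of-life planning statement. It does not remove the point, because the article prints both instruments and they conflict. This is not detail left to an analysis plan, and an unseen plan could not make the printed statements agree.

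Three stronger readings are tempting, and the document supports none of them.

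- A reader might infer that the trial is underpowered for quality of life. Holding the difference at 3.0 points and assuming larger SDs does lower the power: with 176 per group it is 80% at SD 10, 65% at SD 12 and 29% at SD 20. But those SDs are not in the document, and on another score the expected difference may change along with the SD. If the standardised effect of 0.435 carried over, power at 176 per group would be about 98%. If the smaller effect implied by 156 per group carried over (about 0.32), it would be roughly 85%.
- A reader might infer that several SF-36v2 scores will each be tested at 0.05, so that a favourable one could be picked. This rests on a plural noun that can equally mean the patients' scores. The choice of score is also something an analysis plan commonly holds.
- A reader might infer that no SF12 score will exist. The text names only the SF-36v2 as the measure, but it does not rule out an SF12 score derived from it.

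**Conclusion.** The point holds as an internal inconsistency with a calculation error beside it. The planned instrument and the tested instrument differ, so 156 per group at 80% power does not describe the planned quality-of-life comparison. On the SF12's own printed inputs the requirement is about 84 to 85 per group, and 156 would give about 97% power.

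This rests on three assumptions: 6.9 is a common SD of the change, the planned difference is 3.0, and 156 is the quality-of-life figure because that indicator comes last in the list.

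The size of the consequence is small. The 220 per group and the primary endpoint are unaffected. Whether power for an SF-36v2 score is higher or lower than 80% cannot be determined from the document.

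**What to change.** Use one instrument and one score in both Study outcomes and Sample size and statistical considerations. This can be a named SF-36v2 score, or an SF12 score if that is what is intended. In the sample-size paragraph, give that score's expected change in each group and its SD. Replace 156 and 80% with the recalculated size and the power at 220 per group, and at 176 per group if 20% are lost. If the SF12 is kept, either correct 156 or print the inputs that produced it. If no suitable inputs exist, state that quality of life is not powered. In that case the detectable standardised difference of about 0.30 with 176 per group can still be reported.

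The cost is wording in two places and one recalculation, with no change to enrolment on account of this point. The downside is that the quality-of-life power claim may become less favourable or have to be withdrawn.
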